**Fig. 1 Fig1:**
[figure not shown]
Flow diagram showing progress through the study

The trial protocol was approved by the Shanghai Yueyang Integrated Medicine Hospital ethics committee and registered with the Clinical Trial Registry (NCT04462666).

### Patient and public participation

Participants and the public were not involved in the design or recruitment of this clinical trial. In the preparation phase of the trial, we fully considered the time cost of follow-up for each patient. In the data management system, we added an option to upload patient laboratory test reports via a mobile phone and set up treatment follow-up reminders to improve adherence. At the time of signing the informed consent form, participants will be informed of the burden of the study and their freedom to withdraw from the study at any time. Upon completion of the study, all participants will receive feedback concerning the assessment results.

### Eligibility criteria

Inclusion criteria:
(i) Diagnosis of acute gout arthritis as defined by the American College of Rheumatology 1977 preliminary criteria,(ii) Male or non-pregnant, non-nursing female individuals,(iii) 18–70 years of age,(iv) Occurrence of gout attack ≤ 48 h previously,(v) In the week before this observation, non-steroidal anti-inflammatory drugs, analgesic, drugs, and drugs affecting uric acid metabolism were not used,(vi) Subjects capable of providing informed consent,

Exclusion criteria:
(i)Failure to meet diagnostic criteria,(ii)Evidence of uncontrolled concomitant cardiovascular, neurological, hepatic, or gastrointestinal disease—potential participants who have active concomitant disease can only be eligible after discussion and agreement with the treating medical team,(iii)Patients in a critical condition that makes it difficult to evaluate the effectiveness and safety of clinical observations,(iv)Severe deformity, stiffness, and labor loss in patients with advanced arthritis,(v)Known allergy to drugs used in this study.

### Interventions

#### HZG intervention

Participants in the experimental group will receive 10 sacks of HZG granules. They will be instructed to take two sacks per day, one in the morning and one in the evening, approximately 30 min after the meal. The major ingredients of the HZG are listed in Table 1. Placebo etoricoxib will also be administered daily in the morning for 5 days.

#### Etoricoxib intervention

Participants in the etoricoxib group will receive five etoricoxib capsules. They will be instructed to take one capsule per day in the morning, approximately 30 min after eating. The placebo HZG will also be administered two sacks per day, one in the morning and one in the evening, approximately 30 min after the meal.

#### Placebo intervention

Participants in the placebo group will receive 10 sacks of placebo HZG. They will be instructed to take two sacks per day, one sack in the morning and one in the evening, approximately 30 min after the meal. Placebo etoricoxib will also be administered daily in the morning for 5 days.

All patients in each of the treatment groups will be provided free medications and laboratory tests, as well as transportation subsidies, and we anticipate that this will contribute to enhancing patient compliance. During the follow-up of the treatment period, each participant will be requested to record the use of drugs, and they will be advised to return any unused drugs to the hospital during the last follow-up visit.

### Outcome measures

Through the implementation of deterministic, double-blind, double-simulated randomized controlled trials, we can provide clear guidance for the safe management of patients with acute gout. Information from the proposed outcome metrics will be collected for further studies with larger study populations. Recruitment and retention rates, the proportion of patients who do not meet the criteria, and the willingness of patients to be randomly assigned will be calculated. Compliance and compliance rates and qualitative feedback will be checked. Economic data on the use of medical resources and health-related quality of life will be collected and analyzed. Safety outcome measures will be reported in accordance with the requirements of a clinical trial designed to study a drug regimen.

#### Primary outcome

The primary outcome is analgesic effectiveness, assessed as pain in the worst affected joint, which will be measured using the visual analog scale at rest and with activity. The patients will be evaluated from baseline to 5 days post-randomization (4 h, day 1, day 2, day 3, day 4, and day 5) and during the follow-up period. The primary efficacy endpoint will be the assessment of joint pain on treatment days 2–5.

### Sample size

The required sample size was calculated using an estimation formula based on the differences among the three sample rates [14, 17, 18]. A previous clinical study [19] reported that the response rates of the etoricoxib treatment, TCM treatment group, and placebo treatment groups were 63.89%, 42.5%, and 15.5%, respectively. Setting the two-sided significance level (*α*) at 0.05 and statistical power at 0.8, a minimum sample size of 74 participants per group (222 participants in total) was estimated to provide sufficient statistical power to detect a between-group difference of approximately 20% in treatment efficiency, defined as the change in analgesic effectiveness. Considering a 20% loss to follow-up, we aim to enroll 89 patients in each arm, that is, a total of 267 patients.

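### The three-rate formula and the response rates given in the Sample size section do not produce 74 per group, and the stated 80% power fits none of the three comparisons at those rates

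*Protocol article*

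**What the plan says.** All the ingredients stand in one paragraph, under Sample size in the protocol article.

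- Method: an "estimation formula based on the differences among the three sample rates".
- Rates, taken from an earlier clinical study: "response rates of the etoricoxib treatment, TCM treatment group, and placebo treatment groups were 63.89%, 42.5%, and 15.5%, respectively".
- Error rates: "two-sided significance level (*α*) at 0.05" and "statistical power at 0.8".
- Target: enough patients "to detect a between-group difference of approximately 20% in treatment efficiency". The two groups that this difference separates are not named.
- Result: 74 per group (222 in total), raised to 89 per group (267) for 20% loss to follow-up.

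Two other places bear on the reading. The Design section says that the study will test whether HZG is better than placebo. The Statistical analysis section puts all randomised patients in the ITT analysis with last observation carried forward, names a per-protocol analysis of the primary outcomes as a further main analysis, and makes every test two-sided.

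**The concern.** A sample-size paragraph should let a reader get from method and inputs to the printed number. Here the method is a comparison of three rates, three widely separated rates are supplied, and the result is about four times what that method needs. At the same time the power is attached to a difference of about 20 points. The listed rates are 21.4, 27.0 and 48.4 points apart, so the only gap near 20 is etoricoxib versus HZG.

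What is at stake is how the results will be read. The trial has an active-control arm. If the paragraph is taken to give 80% power to every pair, a non-significant difference between HZG and etoricoxib may be read as coming from a comparison sized for it. In the other direction, the paragraph undersells HZG versus placebo, the comparison that the Design section puts forward.

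**Working it through.** **Inputs** (Sample size section): rates 0.6389 (E, etoricoxib), 0.425 (H, taken as the HZG rate) and 0.155 (P, placebo); two-sided α = 0.05, z = 1.960; power 0.80, z = 0.8416; equal groups.

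**Two-group formula** (pooled variance under the null, p̄ the mean of the two rates):

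n = [1.960·√(2p̄(1−p̄)) + 0.8416·√(p₁(1−p₁) + p₂(1−p₂))]² / (p₁−p₂)²

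**1. A route that gives 74.** Take 0.355 versus 0.155, that is, placebo plus 20 points. p̄ = 0.255.

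n = (1.960 × 0.6164 + 0.8416 × 0.6000)² / 0.20² = (1.2081 + 0.5049)² / 0.04 = 73.4, so 74. Power at 74 is 80.3%.

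α, power, the 20-point difference and the placebo rate are all in the paragraph. The rate 35.5% is not, and this is a two-group calculation.

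**2. The named method on the listed rates.** For a 2-df test at 5% with 80% power, the noncentrality is λ = 9.635.

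- Three-group chi-square: p̄ = 0.4063; Σ(pᵢ−p̄)² = 0.1176; p̄(1−p̄) = 0.2412. n = 9.635 × 0.2412 / 0.1176 = 19.8, so 20 per group.
- Arcsine formula, largest versus smallest rate: n = 2λ / (2·asin√0.6389 − 2·asin√0.155)² = 19.27 / (1.8523 − 0.8093)² = 17.7, so 18 per group.

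At 74 per group the three-group chi-square test has more than 99.9% power.

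**3. Pairwise tests on the listed rates**, two-sided 5%, 80% power:

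| Pair | Gap (points) | n per group | Power at 74 |
|---|---|---|---|
| E–H | 21.4 | 84.2 → 85 | 74.6% |
| H–P | 27.0 | 43.1 → 44 | 95.9% |
| E–P | 48.4 | 14.8 → 15 | >99.9% |

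Other two-sided variants do not reach 74 either. E–H needs 82 unpooled, 85 by arcsine and 94 with continuity correction. With continuity correction H–P needs 51 and E–P 19.

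**4. Power for E–H by number analysed.** Power = Φ{[0.2139·√n − 1.960 × 0.7057] / 0.6893}.

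- n = 74: Φ(0.663) = 74.6%. By arcsine it is 74.8%, unpooled 76.1%, and by exact calculation for the uncorrected chi-square test 76.8%.
- n = 71 (89 × 0.8 = 71.2): Φ(0.608) = 72.9%.
- n = 89 (all randomised): Φ(0.921) = 82.1%.

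**The case against.** The strongest answer is that 74 and 80% may both be right. A detectable difference need not equal the gap between two historical rates. A 20-point gain over the 15.5% placebo rate gives exactly 74 at the stated α and power, and it fits the Design section's emphasis on HZG versus placebo. On that reading the power claim is sound and only its description is poor. This stands as a plausible account of what was done. It does not rescue the text: that calculation uses two rates, one of them unprinted, while the paragraph names a three-rate formula. Nor does the match prove the route, because a search over pairs finds others. For example, 42.5% versus 21.1% also gives 74, and so does etoricoxib versus TCM with a one-sided, unpooled, continuity-corrected test (73.2), which contradicts the stated two-sided level.

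A reader might infer something stronger: that the protocol promises 80% power for HZG versus etoricoxib and delivers 75%. The document does not support this. The 80% goes with an unnamed difference. That etoricoxib–HZG is the only listed gap near 20 points makes the inference natural, but it remains an inference. The shortfall also depends on the number analysed. If ITT keeps all 89 per arm, power is about 82%, provided the carried-forward outcomes follow the listed rates. The shortfall returns when only completers count, as in a per-protocol analysis.

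Lower power figures could be obtained with a Bonferroni adjustment over three pairs, but the plan states no such adjustment, so they are not part of this point.

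The cited sources for the formula are not at hand, so its exact form is unknown. Neither of the two three-rate forms tried comes near 74.

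**Conclusion.** The point holds as a mismatch between printed method, printed inputs and printed result. On the listed rates the named approach needs about 18 to 20 per group, roughly a quarter of 74, and no two-sided pairwise test tried gives 74. The figure is consistent with an undescribed comparison of 15.5% with 35.5%. At the listed rates and 74 per group, power is about 75%, 96% and above 99.9%, so 80% describes none of the three comparisons.

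The trial is not shown to be too small for HZG versus placebo; at the listed rates it is better powered than stated. Whether it is short for HZG versus etoricoxib depends on two conditions: that this pair is meant to carry 80% power, and that about 74 or fewer per group are analysed. All of this assumes that the listed rates apply and that the 42.5% TCM rate stands for HZG.

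**What to change.** Keep 267. Replace the Sample size paragraph with the calculation actually used, naming the comparison, the two rates and the formula. If it was a 20-point gain over placebo, the text could read:

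*The sample size is based on HZG versus placebo. With response rates of 35.5% and 15.5%, a two-sided 5% test of two proportions and 80% power, 74 patients per group are needed. At the previously reported rates of 42.5% and 15.5%, 74 per group gives about 96% power. For etoricoxib versus HZG (63.89% versus 42.5%), power is about 75% with 74 evaluable per group, about 73% with 71 and about 82% if all 89 are analysed. We do not claim 80% power for this comparison at 74 per group, and we will report it with a confidence interval.*

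If a different calculation was used, state that one instead and keep the last two sentences. If etoricoxib versus HZG was the intended basis, the text must say that 80% needs about 85 evaluable per group. Bonferroni figures belong in the paragraph only if a multiplicity adjustment is adopted.

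The cost is rewording one paragraph, with no extra patients. The downside is a slightly less favourable printed power for HZG versus etoricoxib. The Trial status section reports 145 patients recruited, so the change should be made and dated before unblinding.

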Our data from clinical studies confirm the effectiveness of HZG in the treatment of GA, with 87.5% of the patients showing improvement in joint swelling and pain. Moreover, HZG can significantly reduce white blood count, erythrocyte sedimentation rate, and C-reactive protein and interleukin-6 levels in patients with GA [14]. However, because of the complex composition of HZG, the mechanism underlying its therapeutic action remains unclear.

The beneficial effects of HZG on acute GA are well known and are considered to be derived from the improvement of wind-dampness-heat syndrome, leading to improvement of joint inflammation. However, no large-scale randomized controlled trials have been conducted on the efficacy, safety, and recurrence control efficacy of HZG. Therefore, we aim to conduct a double-blinded, randomized, controlled clinical trial to evaluate the efficacy of oral HZG for the treatment of patients with acute GA showing wind-dampness-heat syndrome.

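### The sample size and 80% power are worked out for a response rate, but the declared primary endpoint is VAS joint pain on days 2–5, and nothing in the article links the two

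*Protocol article*

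**What the plan says.** **Sample size section.** The number was "calculated using an estimation formula based on the differences among the three sample rates". The rates come from a cited clinical study: "response rates of the etoricoxib treatment, TCM treatment group, and placebo treatment groups were 63.89%, 42.5%, and 15.5%, respectively". With two-sided alpha 0.05 and power 0.8, the section arrives at a minimum of 74 per group (222 in total), enough to "detect a between-group difference of approximately 20% in treatment efficiency, defined as the change in analgesic effectiveness". Allowing for 20% loss, it sets 89 per arm, 267 in total.

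**Primary outcome section.** Analgesic effectiveness is the named outcome. Its definition reads: "assessed as pain in the worst affected joint, which will be measured using the visual analog scale at rest and with activity". It adds: "The primary efficacy endpoint will be the assessment of joint pain on treatment days 2–5". No threshold, percentage reduction or responder rule is given.

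**Elsewhere.** The assessment schedule (Table 2) lists a VAS score and no response variable. The Statistical analysis section lists methods by type of data: t-tests or rank methods for quantitative data, chi-squared and related tests for qualitative data. It does not say which applies to the primary endpoint.

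**The concern.** A power statement is informative only for the variable and comparison for which it was calculated. Here the calculation needs a yes/no response, while the declared endpoint is a pain score. The article contains no rule that turns one into the other, and no VAS mean difference or SD from which power for the score could be worked out.

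Two things are at stake. First, the 80% is the only statement of the trial's sensitivity, and it cannot be checked for the endpoint on which the trial will be judged. Second, with a rate in one section and a score in another, a later report could lead with a VAS difference or with a response rate whose cut-off was chosen after the data were seen, and could cite this article for either.

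**Working it through.** **Step 1. Reproduce the plan's figure.** Inputs from the Sample size section: two-sided alpha 0.05 (z = 1.960), power 0.80 (z = 0.842), a difference of about 20 points, placebo rate 15.5%. Take p1 = 0.355 (placebo plus 20 points) and p2 = 0.155, with mean p = 0.255. The pooled two-proportion formula, 1:1, without continuity correction, is

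n = [1.960 × √(2p(1 − p)) + 0.842 × √(p1(1 − p1) + p2(1 − p2))]² / (p1 − p2)²

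- √(2 × 0.255 × 0.745) = 0.6164
- √(0.355 × 0.645 + 0.155 × 0.845) = 0.6000
- n = (1.960 × 0.6164 + 0.842 × 0.6000)² / 0.04 = 1.713² / 0.04 = 73.4, so 74 per group.

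This is exactly the stated minimum. The match does not prove that this formula was used. The section's own words and inputs are about rates in any case, and no VAS quantity enters.

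**Step 2. Compare the sized quantity with the declared endpoint.**

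| Item | Sample size section | Primary outcome section |
|---|---|---|
| Variable | response, yes or no | VAS pain score, at rest and with activity |
| Time | not stated | treatment days 2–5 |
| Effect | about 20 percentage points | not stated |
| Threshold for response | not stated | not stated |
| SD | not needed for a rate | not stated |

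**Step 3. Sensitivity of the same numbers on the VAS scale.** For a two-arm comparison of means at two-sided 5%, the standardised difference d with 80% power is approximately (1.960 + 0.842) × √(2/n). The last column solves the noncentral t distribution exactly.

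| n per arm | Origin | Approximate d | Exact d |
|---|---|---|---|
| 71 | 89 × 0.8 = 71.2 | 0.470 | 0.473 |
| 74 | stated minimum | 0.461 | 0.464 |
| 89 | all randomised | 0.420 | 0.422 |

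Power with 74 per arm (noncentral t) over a range of assumed true differences:

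| Assumed difference (SD) | 0.3 | 0.4 | 0.5 | 0.6 |
|---|---|---|---|---|
| Power | 44% | 68% | 86% | 95% |

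Nothing in the article places the trial within this range. As an illustration only, an assumed SD of 20 to 30 mm makes 0.46 SD about 9 mm (0.464 × 20 = 9.3) to 14 mm (0.464 × 30 = 13.9).

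**Step 4. Which way does the mismatch cut?** Assume that response is a cut on a normally distributed VAS change with equal variance in both arms. A pair of rates then implies a shift equal to the difference of their normal quantiles. For 35.5% against 15.5% this is −0.372 − (−1.015) = 0.64 SD. A t-test would then have about 97% power with either 71 or 74 per arm. Under that assumption, sizing on the rate is conservative for a continuous analysis.

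**The case against.** The best reply is that the article does make a link. The Sample size section defines treatment efficiency through analgesic effectiveness, which is the name of the primary outcome. On that reading the trial was sized on a response rate derived from the VAS, and the cut-off is a detail left to the analysis plan, which is not shown. This stands in part: the sized quantity was evidently meant to concern the primary outcome. But sharing a name does not turn a score into a rate. The published endpoint is joint pain on days 2–5, and a later plan that made a responder rate primary would be adding to that endpoint, not merely filling in a detail.

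Three stronger readings are tempting and should not be drawn.

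- *The trial is underpowered.* Nothing shows this, and Step 4 of the working points the other way under its assumption.
- *The t-test is the primary analysis, so the power is for the wrong test.* The Statistical analysis section never assigns a test to the primary endpoint. A chi-squared comparison of responders would also fit its list.
- *Response is unstable within the protocol, because the Background gives 87.5% improvement on HZG and the Sample size section 42.5% for TCM.* The figures come from different sources, the second is not stated to be HZG, and the definitions may differ. The comparison proves nothing.

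**Conclusion.** The point holds as a mismatch between two statements in the same article. The 80% power is for a difference of about 20 points in an undefined binary response and is not shown for VAS joint pain on days 2–5. That rests on the text alone.

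How far the true power for the VAS endpoint lies from 80% cannot be determined. The sensitivity figures of 0.47 SD (71 per arm) and 0.46 SD (74 per arm) assume a comparison of two arm means at two-sided 5%. The 97% in Step 4 rests on the normal-shift assumption, and the millimetre range on an SD that the documents do not give. The statement needs correcting because the trial relies on it. The number of patients is not called into question by this point.

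**What to change.** Keep 267 participants. Before unblinding, make the power basis and the primary endpoint match in one of two ways.

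1. **Preferred: restate the sensitivity on the VAS scale.** For example: with 89 randomised and about 71 evaluable per arm, the trial has 80% power at two-sided 5% for a difference of about 0.47 SD in VAS pain between two arms. Convert this to millimetres with an SD from the sponsor's own earlier data or from blinded pooled data in this trial, where the Trial status section reports 145 patients recruited.
2. **If a responder rate is what was sized, define it now.** Fix the VAS change and the day that count as a response, and state whether that rate is primary or secondary.

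The cost is the rewording of one section (plus the Primary outcome section under the second option) and, for the SD, a small blinded calculation. No patients, visits or procedures are added.

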**Methods/design:**

This double-blind, randomized, controlled trial was planned to be conducted between July 1, 2020, and December 31, 2022. A sample size of 267 participants (89 per group) with GA will be randomly assigned to three treatment groups in the ratio of 1:1:1: HZG, etoricoxib, and placebo groups. The study duration is 13 days, including a 1-day screening period, 5-day intervention period, and 1-week follow-up period. The primary outcome is analgesic effectiveness, assessed as pain in the worst-affected joint, which will be measured using the visual analog scale. Secondary outcomes include the patient’s assessment of pain in the primary study joint, patient’s global assessment of response to therapy, investigator’s global assessment of response to therapy, investigator’s assessment of tenderness and swelling of the study joint, and TCM syndromes. Furthermore, the number, nature, and severity of adverse events will be recorded.

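### The 20% loss allowance was applied as 74 × 1.2 instead of 74 / 0.8, so 89 per arm covers about 16.9% loss and leaves about 71 completers against a stated minimum of 74

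*Protocol article*

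**What the plan says.** All the figures stand in one paragraph, the Sample size section of the protocol article.

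- Design values: "Setting the two-sided significance level" "at 0.05 and statistical power at 0.8".
- Target effect: the trial is sized "to detect a between-group difference of approximately 20% in treatment efficiency".
- Size before losses: "a minimum sample size of 74 participants per group (222 participants in total").
- Size after the allowance: "Considering a 20% loss to follow-up, we aim to enroll 89 patients in each arm, that is, a total of 267 patients".

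The Methods/design part of the abstract repeats the result: "A sample size of 267 participants (89 per group"). The Design section gives the total of 267 again.

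The Statistical analysis section decides who is counted. It names an ITT analysis and a per-protocol analysis of the primary outcomes as the main analyses. The ITT analysis takes in every randomized patient, with missing values filled by last observation carried forward (LOCF).

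**The concern.** A loss allowance is meant to leave the required number after the assumed share of enrolled patients has gone. Here it does not. Taken at face value, 89 enrolled per arm with 20% lost leaves fewer than the 74 that the same paragraph calls the minimum. The minimum, the loss rate and the enrolled number cannot all hold.

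What is at stake is the accuracy of the published justification. It claims a 20% margin that the enrolment target does not provide. If losses ran at the planned rate, an analysis restricted to patients with complete data would fall slightly short of its planned size.

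**Working it through.** **Inputs**, all from the Sample size section: required n = 74 per group; loss d = 20%; enrolled n = 89 per arm, 267 in total; two-sided alpha 0.05; power 0.80.

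**1. Reproduce the stated 89.**
- n × (1 + d) = 74 × 1.20 = 88.8, rounded up to 89. This matches, and 89 × 3 = 267.
- n / (1 − d) = 74 / 0.80 = 92.5, rounded up to 93, or 279 in total. This does not match.

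So the plan added 20% of the completers. A loss of 20% is a share of those enrolled.

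**2. What 89 per arm delivers.**
- At 20% loss: 89 × 0.80 = 71.2, about 71 per arm, which is 3 below 74.
- Largest loss that still leaves 74: 1 − 74/89 = 15/89 = 16.9%.
- Check on 93: 93 × 0.80 = 74.4, which keeps 74. The gap in enrolment is 93 − 89 = 4 per arm, 12 in total.

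**3. Effect on power with 71 instead of 74 completers.** The article does not say which pair of rates gave 74, so this was checked in two ways.

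(a) *An assumed pair that reproduces 74.* Take a 20-point difference above the stated placebo rate: p1 = 0.355, p2 = 0.155, mean 0.255. The 35.5% is an assumption and appears nowhere in the article. The usual two-proportion formula is

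n = [1.96 × √(2 × 0.255 × 0.745) + 0.8416 × √(0.355 × 0.645 + 0.155 × 0.845)]² / 0.20²

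= [1.96 × 0.6164 + 0.8416 × 0.6000]² / 0.04 = 73.4, rounded up to 74.

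Power at a given n is Φ[(0.20 × √n − 1.96 × 0.6164) / 0.6000]:

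| n per arm | Power |
|---|---|
| 71 | 78.7% |
| 74 | 80.3% |
| 89 | 87.1% |

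(b) *No choice of rates.* Suppose that 74 gives exactly 80% in a two-sided test. Power at 71 is then Φ[(1.96 + 0.8416) × √(71/74) − 1.96] = Φ(0.784) = 78.4%.

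Both routes put the loss at roughly 1.6 to 1.7 percentage points.

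**4. The stated TCM and placebo rates.** For 42.5% versus 15.5%, the formula in 3(a) needs 44 per arm, and power at 71 is 95.2%.

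**The case against.** A reader might infer that the trial misses its 80% power on its own assumptions. The article does not support that, for four reasons.

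- **The ITT set keeps its number.** It includes all randomized patients with LOCF, so it analyses 89 per arm. On the assumed pair in 3(a), nominal power there is about 87%, provided that imputation does not dilute the effect.
- **The comparison with placebo has room.** On the stated TCM and placebo rates, power is about 95% even at 71 per arm.
- **Loss to follow-up is not the same as loss of the primary endpoint.** The Primary outcome section places that endpoint on treatment days 2–5, and a further week of follow-up comes after. Patients lost in that week may already have supplied their primary data.
- **The rates behind 74 are not stated.** A power figure such as 78.7% belongs to an assumed pair and should not be attributed to the authors.

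A reader might also point to etoricoxib versus TCM, 63.89% against 42.5%, where power at 71 is 72.9%. That pair reaches only 74.6% at the full 74 and needs 85 per arm. Its deficit lies in the base size and is not caused by the loss allowance.

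These arguments limit the consequence but do not remove the error. The paragraph's own allowance treats lost patients as not counting toward 74, and on that footing it falls short. The per-protocol analysis is also one of the two named main analyses. If lost patients leave that set, it would hold at most about 71 per arm at the planned loss.

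**Conclusion.** The arithmetic slip is certain and needs no outside figure: 89 comes from multiplying by 1.2, covers about 16.9% loss, and leaves about 71 per arm at 20% loss, against a stated minimum of 74. It bears on the completer or per-protocol analysis and leaves the size of the ITT set unchanged.

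The consequence is small. Completer power is about 78–79% instead of about 80%. This rests on two assumptions: that 74 corresponds to about 80% power, and that the whole 20% is missing from the completer analysis of the primary endpoint. This is a minor correction to the stated justification and gives no reason to change the design.

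**What to change.** Keep 267 and restate the sentence in the Sample size section, for example:

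*89 per arm allows for up to about 16.9% loss to follow-up; with 20% loss about 71 per arm remain, slightly below the 74 required for 80% power in the completer analysis.*

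The wording should not bring in 35.5% versus 15.5% as if it were the planning assumption. The totals in the abstract and the Design section stay as they are.

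The cost is one corrected sentence and a slightly less favourable stated margin. No additional patients are needed. Keeping the full 20% allowance would mean stating 93 per arm (279 in total), but a loss of under 2 points of completer power does not call for that.
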